#### Patient-level: OTP patients

Eligible patients will be newly initiated on MOUD (within past 30 days) at the participating OTPs and have concurrent stimulant use (indicated by self-report of stimulant use or positive toxicology screen within past 30 days). We focus on patients newly initiated on MOUD because need is highest among these patients: drop-out rates and missed doses are higher during the first 6 months in any subsequent period [5, 6, 32]. Data from these patients will be extracted from the electronic medical record.

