### CM intervention

The CM protocol that will be implemented is Petry’s evidence-based low-cost CM targeting stimulant abstinence [10, 33, 34], which provides immediate reinforcement via prize draws on an escalating schedule. We chose this CM model because of literature supporting better outcomes for patients with stimulant use when: reinforcement is provided immediately [35]; abstinence is the target [36]; and incentive values escalate to promote retention and enhance the patient’s motivation over time [35, 37, 38]. We simplified Petry’s schedule based on formative research with OTP providers who requested simple, weekly draws [13] and a prize system that could be feasibly sourced (i.e., gift cards).

For this study, partner OTPs will administer one random toxicology screen to CM patients per week for 12 weeks. OTPs may choose to test other substances, but reinforcement will be contingent on a negative stimulant result. OTPs may choose which provider (e.g., nurse, counselor) will administer the screen. The CM counselor of record will review the results with the patient.

Patients will earn prize draws for each stimulant negative sample. Draws increase by one for each negative screen for 12 weeks, yielding a maximum of 78 draws for patients who submit 12 negative samples (i.e., 1 + 2 + 3 + 4 + 5 + … + 11 + 12). A refused or missed screen (i.e., unexcused absence on a testing day) resets draws for the next negative sample down to one, with draws again escalating for sustained abstinence. Patients draw prizes from fishbowls containing 500 slips of paper; 250 state “good job!” but are not associated with a prize, 209 state “small,” 40 state “large,” and one “jumbo.” Using these probabilities and magnitudes of $5, $25, and $100 for the three respective prize sizes, each draw has an average cost of $4.21. Thus, for a 12-week protocol, patients maintaining abstinence would be expected to earn an average of 78 draws × $4.21 draw = $328 in prizes. This maximum anticipated earning rate is identical to the rate used by [name] team in the VA rollout [10]. Of note, the average cost of CM in the VA was only $150 per patient, due to missed sessions resulting in resets back to 1 draw [10]. Ensuring OTPs can sustain this investment after removal of support is a key aspect of SSL external facilitation.

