#### EMR extraction and CM tracking tool

OTPs will document CM session delivery in their usual session records within their existing EMR systems and extract a de-identified dataset including all patient encounters at six time points (start and end of each wedge). OTPs will also be given the Excel CM Tracking Tool to facilitate ongoing tracking and provision of real-time feedback, and those OTPs that opt to use the tool will be asked to send the Excel tracker at the same six time points. De-identified data from all available patient records will be identified by each site to allow the study team to calculate key study variables at each OTP including reach, effectiveness (patient abstinence and treatment retention), adoption, implementation, and maintenance.

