### Study measures

To address Specific Aim 1 (implementation effectiveness), we measure the following implementation outcomes: Reach, Adoption, Implementation, Maintenance, and Equity [45]. To evaluate Specific Aim 2 (patient effectiveness), we measure two patient outcomes in line with the Effectiveness element of RE-AIM: Stimulant Abstinence and Treatment Retention. Finally, in pursuit of Specific Aim 3 (exploratory mediators), we evaluate contextual determinants as putative mediators of implementation outcomes; specifically, we assess implementation strategy progress, inner setting factors, and provider characteristics. Table 1 presents a detailed overview of study measures by Specific Aim.

**Table 1 Tab1:** Description of study measures, data source, and timing of measurement

Outcome	Definition	Data source	Frequency and timing of measurement
*Aim 1*			
Reach	Calculates patients’ exposure to contingency management (CM) by dividing the number of newly admitted patients with recent stimulant use (defined as documented patient-reported stimulant use or a positive stimulant urine screen within the first 30 days of treatment) who received 1 or more CM encounters by the total number of newly admitted patients with recent stimulant use.	Electronic medical records (EMR) CM tracking tool	End of each wedge
Adoption	Calculates the proportion of providers who have adopted CM by dividing the number of counselors who delivered 1 or more CM encounters divided by the total number of counselors.	EMR CM tracking tool	End of each wedge
Implementation	Assesses delivery of CM with fidelity in two ways: 1. Proportion of counselors meeting the fidelity target on the CM Competence Scale (a mean overall score ≥ 4.0), which rates 9 CM elements on a scale from 1 (not at all present) to 7 (fully present) 2. Proportion of CM sessions covering ≥ 7 of 9 of the standard CM elements, as assessed by a self-report checklist in the CM tracking tool.	Observer rating CM tracking tool	Role play following Preparation phase End of each wedge
Maintenance	Measures Reach, Adoption, and Implementation throughout the Sustainment phase.	EMR CM tracking tool Observer rating	End of each wedge during Sustainment phase
Equity	Evaluates whether the above systematically vary based on race/ethnicity, biological sex, gender, and other sociodemographic factors of patients and providers.	EMR Provider survey	Baseline
*Aim 2*			

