Stimulant abstinence	Calculates abstinence rates as the number of urine screens that are negative for stimulants divided by the total number of urine screens received by patients with recent stimulant use.	EMR	End of each wedge
Treatment retention	Measures engagement with treatment in three ways for each patient: 1. Duration of time from patient intake to discharge in day 2. Proportion of scheduled encounters that the patient attended 3. Number of CM sessions received	EMR EMR CM tracking tool	End of each wedge
*Aim 3*			
*Implementation strategy progress*			
Stages of Implementation Completion (SIC) [46]	Evaluates completion of key activities for implementing the contingency management intervention across 8 stages. Two scores are calculated for each stage: proportion calculates the percent of activities completed within a stage and duration calculates time from date of entry through completion.	Process notes External facilitator report	Ongoing throughout Preparation and Implementation phase for each OTP
Cost of Implementing New Strategies (COINS) [47]	Calculates the fees, expenses, and person hours necessary to complete the implementation strategy as mapped onto SIC. Customized via a standardized adaptation approach.	Process notes External facilitator report	Ongoing throughout Preparation and Implementation phase for each OTP
*Inner Setting Factors*			
Implementation Climate Scale (ICS) [48]	Measures provider perceptions of the extent to which organizations expect, reward, and support implementation of CM. Scale includes 18 items scored on 5-point scales from 0 (not at all) to 4 (very great extent) divided into 6 subscales.	Provider surveys	Three timepoints for each OTP crossing into active support: Start of Preparation, Midpoint of Implementation, End of Implementation
Implementation Leadership Scale (ILS) [49]	Measures providers’ report of the extent to which leaders at their organization are aligned and visibly in support of CM. Scale includes 12 items, rated from 0 (not at all) to 4 (very great extent) divided into four subscales.	Provider surveys	Three timepoints for each OTP crossing into active support: Start of Preparation, Midpoint of Implementation, End of Implementation

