### Data analysis

Across 2400 EMR pulls, 720, 480, and 1200 are expected to occur during Usual Care, Preparation/Implementation, and Sustainment phases, respectively. Preliminary analysis will include bivariate and multivariate analysis using correlations, cross-tabulations and regression models to ascertain data structure, statistical distribution, and study artefacts. Analyses for all Aims will be performed using multilevel structural equation models (MSEM) in Mplus 8.10 [51]. We conducted Monte Carlo simulation power analyses modeling treatment effects and outcome variance nested in OTPs (anticipated ICC: 15%) and/or counselors (anticipated ICC: 10%; see Table 2). There is no expected missing data from EMR pulls, although at OTP and counselor levels, analyses will follow an intent-to-treat approach to dealing with missing data. Across all analyses, we will employ a moderator-first approach to the equity of treatment effects to ensure that group-level differences can be validly interpreted and that we are sensitive to differential treatment effects among patient subgroups. Similarly, we will examine whether significant variance in treatment effects occurs at counselor- or OTP-levels (through exploring the size of random effects variance parameters) before concluding whether treatment effects can be validly interpreted as fixed at the patient-level.

**Table 2 Tab2:** Results of Monte Carlo simulation analyses examining power to detect aim 1 and aim 2 outcome effects

Outcome	Comparison (*n* per condition)	Predicted rates/effects	Power at α = .05
*Aim 1*			
Reach^a^	Usual care (720)–preparation/implementation (480)	2–22%	98%
Adoption^b^	Usual care (70)–preparation/implementation (70)	10–50%	95%
Implementation	No comparison		
Maintenance	Preparation/implementation (480)–sustainment (1200)		
*Aim 2*			
Stimulant abstinence	Usual care (720)–preparation/implementation (480)	25–40%	90%
Treatment retention	Usual care (720)–preparation/implementation (480)	9 weeks–12 weeks	94%

Monte Carlo simulation multilevel power analyses featuring clustering in opioid treatment programs (anticipated ICC: 15%) and/or counselors (anticipated ICC: 10%)

^a^Assessed among patients nested in counselors and opioid treatment programs

^b^Asssessed among counselors nested in opioid treatment programs

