Aim 1 hypotheses (effect of SSL on CM Reach and CM Adoption) will be tested by examining the effect of treatment condition at a given center at a given time point, for patients nested in counselors in centers (3-level model). Generalized linear mixed models will be used to evaluate treatment effects on rates of CM Reach, Adoption, and Maintenance.

For Aim 2 analyses, generalized MSEM models will be used to model the effect of SSL implementation. Using data from prior CM trials, we assume a rate increase for Stimulant Abstinence from 25 to 40% following SSL receipt, and a treatment retention increase of 30% from 9 to 12 weeks following SSL.

For Exploratory Aim 3 analyses, MSEM models will be used to assess whether putative provider-level mediators that will be assessed via the provider surveys (e.g., implementation climate, implementation leadership, CM perceptions) are associated with change in implementation outcomes. Exploratory outcome analyses will measure putative mediators as latent factors combining measures of SSL fidelity, inner setting factors, and provider characteristics, to assess the extent to which latent factors serve as mechanisms of action for the main effect of the SSL on implementation outcomes using bootstrapped confidence intervals.

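### The abstinence outcome counts the positive screen that qualified the patient, which mainly dilutes the effect and can slightly favour the SSL

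*Protocol article*

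**What the plan says.** Four parts of the protocol article bear on this.

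- **Outcome (Study measures, Table 1, Aim 2).** Abstinence is the count of stimulant-negative screens over the "total number of urine screens received by patients with recent stimulant use". The table gives the end of each wedge as the time of measurement. That says when data are pulled, not which screens count.
- **Population.** The Reach row of Table 1 defines recent use as "documented patient-reported stimulant use or a positive stimulant urine screen within the first 30 days of treatment". The section on patient-level recruitment has the same two routes, "indicated by self-report of stimulant use or positive toxicology screen within past 30 days".
- **Data (EMR extraction and CM tracking tool).** Programs will "extract a de-identified dataset including all patient encounters at six time points", so the qualifying screen is in the data set.
- **Testing and planning.** Under CM intervention, programs give "one random toxicology screen to CM patients per week for 12 weeks". Under Data analysis, "we assume a rate increase for Stimulant Abstinence from 25 to 40% following SSL receipt". Table 2 attaches 90% power to that contrast, with 720 patients in usual care and 480 in preparation/implementation. It predicts reach of 2% and 22% in the same two conditions.

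No section starts the abstinence count after the qualifying screen, after day 30 or at CM start.

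**The concern.** For a patient who enters by a positive screen, the entry criterion and the outcome overlap. The screen had to be positive for the patient to be counted. It then sits in the denominator and can never reach the numerator. It will usually precede CM, because CM is offered to patients already identified as using stimulants.

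Three things follow:

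- With equal testing in both conditions, both rates are pulled down by the same factor and the difference shrinks.
- If patients under the SSL have more later screens, the fixed failure weighs less there, and the scored rate rises with no change in use.
- Patients who qualify by self-report alone carry no fixed failure, so a shift in the mix of routes between phases moves the endpoint.

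The first effect remains even if every patient is scored individually on an identical testing schedule.

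**Working it through.** **The plan's own figure.** A two-proportion calculation at 25% v 40% with 720 v 480 independent patients gives 99.98% power (two-sided, alpha 0.05). With counselor clustering (ICC 0.10, design effect 1 + (m − 1) × ICC), it gives 92.3% at m = 1200/70 and 75.1% at m = 2400/70. Treating the 15% program-level ICC as in a parallel design gives 15% to 42%; a rough stepped-wedge calculation gives about 99%. The stated 90% lies inside this range, but the simulation settings are not given, so it is neither confirmed nor refuted. A design effect of 2.86 returns 90% and serves below only as a reference point.

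**Formula.** Let n be the later screens per patient, q the average number of fixed positives per patient, and p the true negative rate on later screens. Then

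scored rate = p × n / (n + q).

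Here q = 1 if all patients qualify by screen with one positive, 0.5 if half do, and 2 if each has two positives before CM. The article gives neither n nor q; the values below are assumptions.

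**Dilution, equal testing, true 25% v 40%.** Power is at the reference design effect (about 720/2.86 = 252 v 480/2.86 = 168 effective patients).

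| n | q | Scored rates | Difference (points) | Power |
|---|---|---|---|---|
| no fixed positive | 0 | 25.0 v 40.0% | 15.0 | 90% |
| 3 | 1 | 18.8 v 30.0% | 11.3 | 76% |
| 4 | 1 | 20.0 v 32.0% | 12.0 | 79% |
| 12 | 1 | 23.1 v 36.9% | 13.8 | 86% |
| 12 | 0.5 | 24.0 v 38.4% | 14.4 | 88% |
| 20 | 0.5 | 24.4 v 39.0% | 14.6 | 89% |

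**False gain, no true effect (25% in both conditions), 3 later screens without CM and 12 with it.**

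- Upper illustration, every SSL patient screened weekly for 12 weeks and no usual-care patient. With q = 1: 0.75/4 = 18.8% v 3/13 = 23.1%, or 4.3 points. With q = 2: 0.75/5 = 15.0% v 3/14 = 21.4%, or 6.4 points.
- At 2% v 22% reach, each patient scored separately: (0.22 − 0.02) × 4.3 = 0.9 points (q = 1) and 0.20 × 6.4 = 1.3 points (q = 2).
- At the same reach, screens pooled. Mean later screens are 0.98 × 3 + 0.02 × 12 = 3.18 in usual care and 0.78 × 3 + 0.22 × 12 = 4.98 under the SSL. With q = 1: 0.25 × 3.18/4.18 = 19.0% v 0.25 × 4.98/5.98 = 20.8%, or 1.8 points. With q = 2: 0.25 × 3.18/5.18 = 15.3% v 0.25 × 4.98/6.98 = 17.8%, or 2.5 points.

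**Mix of routes.** At n = 12 and p = 25%, moving from all patients to half qualifying by screen changes the scored rate from 23.1% to 24.0% with no change in use.

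**The case against.** **It is a condensed article.** Table 1 gives a one-line definition, and a full protocol or analysis plan, not shown, may set the window. This would answer a complaint of missing detail. But Table 1 states numerator, denominator and population, and its denominator is the total of screens received. A later document that dropped the qualifying screen would change that rule, not fill a gap.

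**The larger figures are tempting but not supported.** A reader might infer a false benefit of 4 to 6 points. That needs every SSL patient to have 12 later screens. Weekly screening applies to CM patients only, predicted reach is 22%, and one CM encounter is enough to count as reached. This objection stands, and only the smaller range can be defended. Patients who qualify by self-report reduce it further.

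**The directional bias comes from unequal testing.** Correct. With equal testing only dilution remains, which is conservative and cannot create a benefit.

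**The strongest dilution is an extreme case.** It needs 3 later screens and all patients qualifying by screen. If the 25% and 40%, taken from prior CM trials, were themselves computed over all screens, the planned difference does not shrink. Both points stand and are carried as assumptions.

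**The qualifying screen may follow CM start.** The window covers 30 days and no CM start day is fixed, so the screen usually precedes CM but need not.

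**Conclusion.** The point holds as a flaw in a stated outcome rule: for screen-qualified patients, one scored screen is a failure by definition.

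The main consequence is dilution of the 15-point difference to about 11 to 14.6 points. This rests on 25% and 40% being rates on later screens, on 3 to 20 later screens per patient, and on half to all patients qualifying by screen. A false gain for the SSL is possible but smaller, about 1 to 2.5 points at 2% v 22% reach, with 3 v 12 later screens and all patients qualifying by screen.

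The article does not support the inference that an SSL effect on abstinence would be mostly artefact, or that the stated 90% power has been shown wrong. Abstinence is a secondary (Aim 2) outcome, so the primary implementation aim is untouched. The definition should still be corrected, since the article reports that no programs or providers had been enrolled.

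**What to change.** In Table 1, define stimulant abstinence on screens collected after the date the patient first met the recent-use criterion: the qualifying screen, or the documented self-report if that came earlier. Use one stated follow-up window from that date, the same in every phase. Include the qualifying route (positive screen v self-report only) as a baseline covariate.

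The all-encounter extract should already hold the results needed, so no new collection is expected. There are two costs. Screens before the time origin, including any genuine early negatives, are dropped. Patients with no later screen have no outcome; because this may depend on retention, itself an Aim 2 outcome, their number should be reported by condition with a sensitivity analysis. The common window does not by itself equalise testing frequency between conditions.

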The SSL has demonstrated effectiveness in promoting the implementation of CM targeting attendance [20], but has never been evaluated for the implementation of CM targeting stimulant use. Furthermore, prior SSL studies have been subject to several limitations. First, previous investigations have confounded receipt of the SSL implementation strategy with provision of CM resources by providing OTPs a fully stocked prize cabinet at the start of implementation [20, 21, 24]. Second, SSL trials have only measured sustainment for up to 6 months [24], which limits conclusions about the ability of OTPs to continue CM implementation without active support. Finally, studies of the SSL have not rigorously tracked adherence to implementation strategy [20, 21, 24]. The current project will address these three gaps by: decoupling the SSL strategy from the provision of incentives; using a stepped wedge design that enables monitoring of sustainment over a longer time horizon; and rigorously specifying and tracking the SSL strategy.

Our protocol is guided by three specific aims:Specific aim 1 (primary aim): to test the effectiveness of the SSL on implementation outcomes. It is hypothesized that receipt of the SSL will be associated with significant increases in: CM Reach (percent of patients receiving CM), CM Adoption (percent of providers delivering CM), and CM Maintenance (reach and adoption after removal of active support).Specific aim 2 (secondary aim): to test the effectiveness of the SSL on patient outcomes. It is hypothesized that receipt of the SSL will be associated with significant increases in: Stimulant Abstinence (percent of stimulant-negative screens) and Treatment Retention (number of treatment sessions).Specific aim 3 (exploratory aim): to evaluate contextual determinants, including SSL adherence, as putative mediators of implementation outcomes. It is hypothesized that contextual factors at the organization-level (e.g., implementation climate, leadership) and provider-level (e.g., perceptions of CM) will partially explain the effect of the SSL on implementation (Aim 1) outcomes.

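### The Aim 2 retention outcome is described inconsistently, and one of its three measures counts CM delivered rather than time in treatment

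*Protocol article*

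**What the plan says.** The protocol article describes retention in three places.

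- **Background, specific aim 2.** The hypothesis is an increase in "Treatment Retention (number of treatment sessions").
- **Study measures, Table 1, Aim 2.** Retention has three measures. The first is a length of stay, given as "Duration of time from patient intake to discharge in day". The second is the share of a patient's booked visits that were kept. The third is the item "Number of CM sessions received". None is named as the main measure, and no rule for combining them is given.
- **Data analysis and Table 2.** The assumed effect is "a treatment retention increase of 30% from 9 to 12 weeks following SSL". Table 2 gives 94% power for this with 720 usual-care and 480 preparation/implementation EMR pulls.

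Reach, an Aim 1 outcome, is the number of newly admitted patients with recent stimulant use "who received 1 or more CM encounters by the total number of newly admitted patients with recent stimulant use". Table 2 expects it to go from 2% to 22%. Under CM intervention, "partner OTPs will administer one random toxicology screen to CM patients per week for 12 weeks".

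**The concern.** The three descriptions do not name the same quantity. The count of treatment sessions in the hypothesis is not among the three Table 1 measures, and only the first of those corresponds to the weeks used for power.

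The third measure is the more serious problem. Whether a patient has any CM sessions depends first on whether the program is delivering CM, and that is what the SSL is designed to change. In a comparison of SSL with usual care, the measure therefore follows Aim 1 implementation, whatever happens to patients' time in treatment. Under Study design, the protocol justifies collecting patient outcomes on the ground that good implementation need not bring better patient outcomes. A count of CM sessions cannot separate those two things. With no main measure named, retention could be reported as improved on this count when duration shows no change.

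**Working it through.** **1. The plan's own retention figure.** Table 2 states 94% power for 9 against 12 weeks, 720 against 480, α = 0.05 (two-sided assumed). No SD is given, and the text does not say which ICCs entered the retention row, so the figure can be neither confirmed nor refuted. The SD it implies is

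SD = 3 / [(1.960 + 1.555) × √(1/720 + 1/480)] = 3 / (3.515 × 0.0589) = 14.5 weeks without clustering.

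Dividing by the square root of a design effect, with 1,200 pulls over 10 OTPs (120 each) and 70 counselors (17.1 each):

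- counselor ICC 10%: 1 + 16.1 × 0.10 = 2.61, so SD = 9.0 weeks;
- OTP ICC 15%: 1 + 119 × 0.15 = 18.85, so SD = 3.3 weeks. This is a worst case, because OTPs cross over and within-OTP contrasts recover information.

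The powered quantity is time in treatment, and the point below does not depend on the 94%. As a minor matter, 12/9 − 1 = 33%, not 30%.

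**2. Inputs for the CM-session count.** Reach is 2% and 22% (Table 2). The maximum is about 12 sessions, inferred from one screen a week for 12 weeks. Let k be the mean number of CM sessions among patients reached. The document does not give k, and it is assumed equal in both conditions.

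**3. Expected count per patient, with identical time in treatment.** Mean = Reach × k.

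| k (assumed) | Usual care (0.02k) | SSL (0.22k) | Ratio |
|---|---|---|---|
| 1 | 0.02 | 0.22 | 11 |
| 3 | 0.06 | 0.66 | 11 |
| 6 | 0.12 | 1.32 | 11 |
| 12 | 0.24 | 2.64 | 11 |

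The ratio is 0.22/0.02 = 11 for any common k. About 0.98 × 720 = 706 usual-care patients would score zero, against 0.78 × 480 = 374 under SSL.

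**4. Simulation with no effect on stay.** Each scenario had 1,000 simulated trials of 10 OTPs, with 72 usual-care and 48 SSL patients per OTP. Stay followed the same distribution in both conditions (mean about 9 weeks), Reach was about 2% and 22%, and attendance at weekly CM sessions was 30%, 60% or 90%. Scenarios were run with and without variation between OTPs. A paired site-level t test was significant for the CM-session count in 99.8% to 100% of trials, and for duration in 4.1% to 5.3%, about the nominal 5%. This is not the planned multilevel model. It shows only that the difference in Reach carries straight into the count.

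**The case against.** The strongest defence is that nothing in the article says the CM-session count will decide the retention hypothesis. The hypothesis refers to treatment sessions rather than CM sessions, the only stated effect is in weeks, and two of the three Table 1 measures can be taken in any period without reference to CM. That stands. The risk is conditional on the count being tested or reported as retention.

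A reader might also infer several stronger things that the document does not support.

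- *The count is zero in usual care by construction.* Table 2 expects Reach of 2% and Adoption of 10% in usual care, and the Discussion says all sites get a one-hour CM webinar. The count is expected to be low, not fixed at zero.
- *The count merely repeats Reach.* Reach is one or more encounters. The count also reflects how long recipients persist with CM. The 11-fold ratio is the Reach ratio carried over under equal k.
- *Any count of treatment sessions rises mechanically because CM adds visits.* The document does not say that CM visits are additional. CM is documented in usual session records and is meant to be integrated into the usual workflow, so it may use existing contacts.
- *Duration is faulty because some patients are not yet discharged at a data pull.* Their handling is commonly left to the SAP, which is not shown, and is not an error here.

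Finally, retention belongs to a secondary aim of a trial that puts implementation outcomes first.

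**Conclusion.** The point holds in limited form. Retention is described inconsistently across the aims, Table 1 and the power statement. One of its three measures is exposure to CM, which cannot by itself show patient benefit in a comparison of SSL with usual care. At the protocol's own Reach, that measure would differ about 11-fold with no change in time in treatment, assuming equal sessions per recipient. A different k in the two conditions would change the ratio, but not the fact that Reach drives it.

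The document does not support saying that the trial will find improved retention whatever happens to patients. That would require the CM-session count to be used as the retention result, which the current wording permits but does not state. Days in treatment and the proportion of scheduled encounters attended do not share the defect. Stimulant abstinence and the primary aim are untouched. The correction should be made, because it is cheap and protects one of the two Aim 2 outcomes.

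**What to change.** 1. Name time from intake to discharge as the Aim 2 retention outcome, matching the weeks in the Table 2 power row.
2. Keep the proportion of scheduled encounters attended as a supportive measure.
3. Move the number of CM sessions received to Aim 1 as a dose measure, described among patients who start CM, and do not present it as a patient outcome.
4. Align the aim 2 hypothesis, Table 1, the Aim 2 analysis text and Table 2 on this definition, and reconcile the stated 30% with 9 to 12 weeks.

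The SAP can state how patients still in treatment at a data pull are handled. Censoring them at the pull is a sensible choice. If that changes the model from the one simulated, the 94% should be rerun.

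The cost is wording and, at most, one repeated power simulation. All three quantities are already to be collected, and Trial status reports that no organization or provider had yet been enrolled.
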